## Introduction

### Background and Rationale

Mental health disorders are common in the general population. In Chile, depression and anxiety are the most frequently observed psychopathologies, with a prevalence of 5% for depression and 6.5% for any form of anxiety [1]. However, the population affected by depression or anxiety symptoms may be greater, with 49.2% of Chileans reporting some level of depression symptoms [2]. These prevalences have become a significant issue in public health settings, where waitlists in public mental health services in Chile are mostly stagnant [3], and in the past 2 years have become extensive due to the COVID-19 pandemic. Thus, it becomes necessary to find alternatives that allow providers to respond to this need for mental health access [4].

In this context, the use of remote self-guided psychological interventions, such as those found in mental health mobile apps, has gained popularity [5]. It has been reported that this remote modality improves access, reduces waiting times for appointments, saves time, and reduces the effect of attitudinal barriers in patients seeking psychological support [6]. Studies indicate a high effectiveness rate of web-based care, with smartphone-based psychological interventions reducing user anxiety [7] and depression [8,9]. Accordingly, there has been an increased number of mental health mobile apps available to users. However, many of them do not have sufficient theoretical support for their effectiveness. In 2015, a total of 447 apps related to cognitive behavioral therapy (CBT) were found available in any App Store [10]. Conversely, 9 studies regarding the use of smartphones in cognitive-behavioral interventions were found, of which only 2 had readily available apps in the market [10]. Moreover, 10% of those who say they use cognitive behavioral interventions as a theoretical basis were not evidence-based [11]. It has been suggested that, without empirical support, these apps can be potentially harmful to users [12].

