Among the small portion of mobile apps that have empirical support for their tools, 3 specific components or modules have the highest rates of applicability and effectiveness for reducing depression and anxiety: assessment, education, and self-regulation digital tools [13]. The assessment component allows for the recognition of the current symptomatic state of the user, while the constant evaluation helps the monitoring and the development of awareness of the process of change in the symptomatology [14]. The psychoeducation process allows users to be informed about what they are experiencing. Although psychoeducation alone is an effective strategy for the improvement of some anxiety and depression symptoms [15,16], its effectiveness increases when it is accompanied by other strategies [17]. The final component, the use of self-regulation tools, demonstrates a series of brief, easy-to-use self-guided activities that attempt to regulate, express, or otherwise manage psychological distress, low mood, and symptoms of anxiety.

The presentation of these modules normally follows the theoretical framework of CBT. This treatment model can be easily adapted to non–face-to-face environments and has been repeatedly tested in web-based modalities [18,19]. Moreover, other approaches theoretically derived from CBT, such as behavioral activation therapy or mindfulness-based behavioral therapy, also exhibit evidence of their effectiveness in non–face-to-face settings [20]. The behavioral activation treatment for depression attempts to regulate depression symptoms through the programming of pleasurable activities [21], while mindfulness-based CBT focuses primarily on breathing techniques, relaxation, self-compassion, and mindfulness abilities [22], aimed at regulating anxiety states.

According to the literature, there are no mobile apps with scientific support to address depression and anxiety symptoms in the adult population in Chile. The regular and widespread use of such apps could help provide self-care tools to individuals who are reticent about therapy.

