### Eligibility Criteria

Adult Chilean citizens, 18 years of age or older, with access to a computer, tablet, or smartphone (Android or iOS) with internet, and no untreated mental health diagnosis, will be included in the study. The mental health diagnosis and current treatment will be assessed solely by the participant’s self-report.

Individuals who self-report substance abuse problems or any current serious mental health disorder and participants reporting scores greater than 1 on question 9 (suicidal ideation) on the Patient Health Questionnaire–9 (PHQ-9) will be excluded from the study.

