### Outcomes

#### Primary Outcomes

Anxiety symptom is 1 of the 2 primary outcomes, and it will be measured by the Generalized Anxiety Disorder–7 Scale (GAD-7). It consists of 7 items that the person assesses on a scale of 0-3 according to the frequency with which each symptom has disturbed them during the past 2 weeks [23]. It shows high reliability in Chilean samples (Cronbach α=0.86 [24]).

Depression symptoms will be measured by the PHQ-9 depression scale, which consists of 9 items that evaluate the presence of depression symptoms present in the past 2 weeks, with a response scale of 0=never, 1=some days, 2=more than half the days, and 3=almost every day. With a Cronbach α of 0.83, its reliability is high in Chilean samples [25]. Additionally, depression and anxiety symptoms in the past week will be assessed through the Patient Health Questionnaire–4 (PHQ-4) [26].

Primary and secondary outcomes will be assessed at 3 time points: preintervention (baseline), immediately post intervention (30 days post intervention), and 1-month follow-up in all groups.

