### Data Collection and Management

#### Plans for Assessment and Collection of Outcomes

Self-report questionnaires assessing primary and secondary outcomes will be administered at baseline (immediately before intervention), post intervention, and follow-up. Primary outcomes will be assessed through the website and the app, and secondary outcomes will be measured only on the website.

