#### Adverse Event Reporting and Harms

The intervention does not cause any harm to the participants. However, if participants experience emotional distress upon using the app, they can contact the lead investigator at any time, who can provide them with options for referral to other public mental health services available. This procedure is explained in detail in the informed consent and initial training videos.

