## Discussion

### Overview

This study aims to develop a multiplatform self-help mental health mobile app for adults and test the effectiveness of its modules post intervention and at 1-month follow-up. This is the first study in Chile to develop and test the effectiveness of a mobile app to manage anxiety and depression symptoms in adults. The intervention proposed is based on evidence suggesting that the internet or remote intervention tools and self-management of prevalent symptomatology could be the future of mental health care systems in the digital era. If the effects of the intervention are positive, wide implementation in Chile and other Spanish-speaking countries could be possible in the future.

However, this project faces some challenges regarding feasibility and adoption of the intervention, where dropout rates could potentially hinder the results of the experimental procedure, even when accounted for [36]. Additionally, probable limitations are the exclusion of part of the clinical population from the study sample (ie, individuals not currently in treatment or at suicide risk) and the difficulty of controlling the effects of therapy on the primary outcomes in individuals simultaneously undergoing psychotherapy.

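### The harms procedure, as stated, gives no response when a participant's PHQ-9 item 9 score after enrolment exceeds the level that bars entry

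*Protocol article*

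**What the plan says.** All references are to the Protocol article.

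- **Entry.** Eligibility Criteria excludes people with "scores greater than 1 on question 9 (suicidal ideation") on the PHQ-9. The Discussion (Overview) lists as a limitation the loss of part of the clinical population, described as "individuals not currently in treatment or at suicide risk".
- **Repeat collection.** The PHQ-9 is one of two primary outcome scales. Under Primary Outcomes, "Primary and secondary outcomes will be assessed at 3 time points": baseline, the end of the 30-day intervention, and one month later. Under Plans for Assessment and Collection of Outcomes, "Primary outcomes will be assessed through the website and the app", by self-report.
- **Harms.** Adverse Event Reporting and Harms opens with "The intervention does not cause any harm to the participants". It then gives one route: "if participants experience emotional distress upon using the app, they can contact the lead investigator at any time". The lead investigator can then offer referral to public services. The section adds that the consent form and training videos explain this procedure in detail.

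**The concern.** The trial sets its own threshold for a worrying answer and acts on it once, at the door. It then asks the same question twice more, with no clinician present. The stated harms route does not depend on that answer. It depends on the participant deciding to make contact, and its wording ties the distress to use of the app. Someone whose suicidal ideation has another cause, or who reports it at follow-up after the 30-day access period, does not clearly fall within it.

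The flat assertion of no harm adds to this. It states as a premise something the trial has yet to observe, and a harms section built on it gives no reason to record events.

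At stake is participant safety and the trial's ability to report harms. The treatment comparison is not at stake.

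**Working it through.** The article gives no figure on this point to reproduce, so the check is a comparison of sections.

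**Step 1: is the disqualifying answer collected again?** Yes. There are 3 scheduled PHQ-9 time points. Taking the baseline one as the entry screen, 3 − 1 = 2 come after it. The missing-data section says the app will not let a user proceed with an incomplete questionnaire, so an item 9 answer given in the app cannot be skipped.

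**Step 2: does any section state a response to it?** I read each section where one could appear.

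| Section | What it provides | Triggered by an item 9 answer? |
|---|---|---|
| Eligibility Criteria | Exclusion at entry | At entry only; no step for later scores |
| Criteria for Discontinuing or Modifying Allocated Interventions | Leaving at the participant's own wish | No |
| Data Management | Coded data; lead investigator, assistants and statistician have access | Review of answers not described |
| Interim Analyses | None planned | Not relevant to case review |
| Composition of the Coordinating Center | Daily support, weekly team meetings | Review of answers not described |
| Data Monitoring Committee; Auditing | Yearly check of files and completeness | No |
| Adverse Event Reporting and Harms | Participant-initiated contact | No |

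No section states an alert, display, contact, referral or withdrawal tied to a later score.

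**Step 3: does the stated route cover the case anyway?** Only if the participant makes contact and sees the distress as arising from the app. Under Trial Design, access lasts 30 days, so the 1-month follow-up PHQ-9 falls after that period.

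**Step 4: does the no-harm sentence fit the rest of the article?** Poorly. Results says recruitment has not begun, so no safety data from this trial exist. Background and Rationale reports the suggestion that "without empirical support, these apps can be potentially harmful to users" and says that "there are no mobile apps with scientific support to address depression and anxiety symptoms in the adult population in Chile". Neither statement shows that this app is harmful, but both sit badly with declaring it harmless beforehand.

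**Step 5: scale.**
- Post-enrolment item 9 answers with no stated response: 196 × 2 = 392 with full retention. With the 36 per arm retained in the sample size section: 36 × 4 × 2 = 288.
- People giving an answer above 1: unknown. As an assumption only, not from the article, take 0.5% to 3% of participants doing so at least once. With 26% dropout, 196 × 0.74 = 145 remain, and 0.005 × 145 = 0.7. With no dropout, 0.03 × 196 = 5.9. That spans from under one person to about six, and the entry exclusions push towards the low end.

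**The case against.** The strongest reply is that a journal article condenses a longer protocol, and that a risk-response procedure is just the kind of operational detail left there. Dissemination Plans refers to a full protocol, the consent form and training videos are not shown, and the ethics committee approved the associated documents. A participant-initiated route does not rule out a score-triggered one. This stands as a limit: a reader might infer that the trial has no suicide-risk procedure at all, and the documents do not support that. It does not remove the point, because the harms section makes a positive claim and specifies a route, and both can be judged as written.

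A reader might also infer that nobody sees an answer until the trial ends. The article does not say so. The interim analysis section concerns statistical analyses, while other sections give the lead investigator database access, daily support duties and weekly meetings. What can be said is that none of these is described as reviewing individual answers.

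Nor does the article's rationale amount to calling this app harmful. The warning about unsupported apps is introduced as a suggestion, the same section credits the three component types with evidence of effectiveness, and the sentence after the no-harm claim allows for distress. The fault is an unqualified assertion, not a direct contradiction.

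Finally, the remedy is partial: an on-screen referral list still needs the participant to act. That is true, but the information then reaches everyone who gives the answer, without their having to ask.

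**Conclusion.** The point holds in a limited form. The article bars entry on an item 9 score above 1, collects the same item remotely twice more, and states a harms procedure under which that answer, after enrolment, prompts nothing unless the participant makes contact. It also asserts an absence of harm that has not been shown.

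The number of people affected is unknown, and the illustrative range above should not be read as an estimate. Estimand, analysis and power are untouched. The conclusion assumes that the baseline PHQ-9 serves as the entry screen and that the harms section describes the operating procedure. If the full protocol already contains a score-triggered step, what remains is to state it in the harms section. This is a cheap safety improvement worth making, not a flaw in the trial's validity.

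**What to change.** Amend Adverse Event Reporting and Harms in three ways.

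1. Any post-enrolment PHQ-9 with item 9 above 1 (or a lower score set by the sponsor and ethics committee) automatically shows a fixed, ethics-approved list of crisis and public mental health referral options plus the investigator contact. The display is identical in all arms, on website and app, and each event is logged for reporting by masked arm.
2. Word the contact route to cover any distress during participation, whatever its cause.
3. Replace the no-harm sentence with a statement that harms will be recorded.

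**Cost.** The list must be written and approved. A display rule and a log field must be programmed in each group's app version, on iOS and Android, and on the website. The amendment must be notified to the ethics committee. The display needs no extra staff, re-identification or unblinding.

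**Downside.** Shown post intervention, the list may slightly raise help-seeking before the 1-month follow-up. The rule is the same in every arm, but exposure to it could differ if trigger rates differ. The logged counts by masked arm would show whether that happened.

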#### Frequency and Plans for Auditing Trial Conduct

A monitor from the Ethical Scientific Committee will check annually the presence and completeness of the investigation files, such as informed consent, inclusion and exclusion criteria, and data collection and storage.

#### Plans for Communicating Important Protocol Amendments to Relevant Parties (eg, Trial Participants and Ethical Committees)

All substantial amendments will be notified to the Ethics Committee of the Universidad de Talca. In case amendments concern or affect participants in any way, they will be informed about the changes. If needed, additional consent will be requested and registered. Additionally, web-based trial registries will be updated accordingly.

#### Dissemination Plans

All results of this research will be disclosed completely in international peer-reviewed journals. Executive summaries of the results will be given to government authorities and public entities acting as stakeholders. Lastly, preliminary relevant results will be presented at an international internet-based mental health seminar organized by the research team, to take place in mid-2024. The full protocol will be made publicly available on the original registry’s website when the study is completed. Publications resulting from this protocol will consider the principal investigators and any participating analyst as authors.

## Results

The trial is not yet recruiting and is expected to end in October 2024. The first results are expected in late April 2024.

## Discussion

### Overview

This study aims to develop a multiplatform self-help mental health mobile app for adults and test the effectiveness of its modules post intervention and at 1-month follow-up. This is the first study in Chile to develop and test the effectiveness of a mobile app to manage anxiety and depression symptoms in adults. The intervention proposed is based on evidence suggesting that the internet or remote intervention tools and self-management of prevalent symptomatology could be the future of mental health care systems in the digital era. If the effects of the intervention are positive, wide implementation in Chile and other Spanish-speaking countries could be possible in the future.

However, this project faces some challenges regarding feasibility and adoption of the intervention, where dropout rates could potentially hinder the results of the experimental procedure, even when accounted for [36]. Additionally, probable limitations are the exclusion of part of the clinical population from the study sample (ie, individuals not currently in treatment or at suicide risk) and the difficulty of controlling the effects of therapy on the primary outcomes in individuals simultaneously undergoing psychotherapy.

### Conclusion

Implementing this research protocol, we expect to provide evidence for the effectiveness of a mental health mobile app in reducing depression and anxiety symptoms in Chilean adults. Moreover, we expect to provide evidence on the associations of these symptom variables and other risk or protective factors for mental health in adults in the context of digital platforms and interventions for health. The potential clinical and research implications derived from this study could help the mental health and well-being of the Chilean population significantly.

## Abbreviations

BRS: Brief Resilience Scale
CBT: cognitive behavioral therapy
ERQ: Emotional Regulation Questionnaire
GAD-7: Generalized Anxiety Disorder-7 scale
MAAS: Mindfulness attention awareness scale
MMRM: mixed model for repeated measures
PHI: Pemberton Happiness Index scale
PHQ-4: Patient Health Questionnaire-4
PHQ-9: Patient Health Questionnaire-9
RRS: Ruminative Response Scale
